The participants are instructed to wear the Apple Watch for at least 18 hours per day during the 12-week observation period. Apple Health Kit data are collected, uploaded, and stored through the third-party digital health and research platform. Metrics of interest include those related to respiratory function (eg, respiratory rate), heart activity (eg, heart rate, heart rate variability), physical activity (eg, steps, bouts of activity, standing time), sleep (eg, in-bed time, sleep phases), and mobility (eg, gait speed, walking asymmetry, step length) (Table 1). Survey completion rate and adherence to required watch wear times are monitored by the study team. Participants receive notifications from the study team to encourage high levels of adherence based on completion standards selected a priori (eg, number of daily check-ins completed each week and daily and nightly hours of wear). Participants receive weekly monetary incentives for completing each component of the study, with up to US $210 total. Those who do not meet adherence standards may not be eligible to receive a given week’s compensation. Furthermore, those consistently not meeting standards within the first few weeks of the study may be withdrawn in an effort to allocate research team time to adherent participants and prevent excessive amounts of missing data. At the end of the 12-week observation period, the participants complete an additional battery of discharge surveys, once again deployed through the third-party app (Table 1). They also complete a series of task-based measures prior to study discharge.

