### Analysis Plan

#### Outcome Measures

A digital biosignature will be developed to enable the detection of a change in pain status. The primary outcome used to validate the biosignature (ground truth) will be the participant’s self-reported onset of a pain flare. Additional models will be explored to predict secondary outcomes such as a clinically relevant change in pain interference, namely, 2 units on the Pain, Enjoyment of Life, and General Activity (PEG 3-item) scale or the onset of pain flares lasting for more than 2 days only. To improve pain flare prediction, participants may be stratified by demographic features known to impact the pain experience, and models may be adjusted using partial correlation. Accounting for individual factors may be particularly relevant when considering differences in digital access and literacy among participants residing across diverse geographic locations.

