#### Data Reduction

Raw physiological signals (eg, heart activity, step counts, sleep stages) will be synchronized across modalities and aligned to a common timeline while preserving native sampling frequencies. To capture information across temporal scales, features will be engineered using a *multiresolution aggregation strategy*. For each signal, summary statistics will be computed over short windows (seconds to minutes) and further aggregated into intermediate (hourly) and daily summaries. All features derived at finer resolutions will be consolidated into a single daily feature vector, enabling the integration of short-term variability and longer-term physiological trends. The model prediction target and evaluation will be defined at a chosen time scale (eg, daily). Any windowing will only use past data relative to the prediction time to avoid leakage.

In addition to static summaries, *dynamic features* will be generated to characterize within-day temporal structure and behavior. These may include acceleration-based metrics (eg, mean acceleration), measures of temporal change (eg, slopes and rates of change), and circadian rhythm features. Complexity metrics (eg, entropy-based measures) may also be included to quantify signal regularity.

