#### Handling Missing Data

Missing data due to nonwear or sensor dropout will be handled using a hierarchical approach. Short gaps will be interpolated when physiologically appropriate, whereas longer gaps will be left missing at the raw level. Daily features may be imputed using time-series–aware methods (eg, forward/backward filling within individuals). Missingness indicators will be included as additional covariates in model development to account for information loss.

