#### Biosignature Development

Higher-level multivariate models will be developed, beginning with simpler traditional machine learning models before progressing to deep representation learning methods. Traditional machine learning algorithms will be trained using a nested k-fold cross-validation design. Model performance will be assessed using the area under the receiver-operator characteristic curve (AUROC), the area under the precision-recall curve (AUPRC), the *F*_1_-score, Spearman Rho, and/or Mann-Whitney tests of prediction outputs. Additionally, deep learning algorithms will be trained using train/validate/test sets where model loss, AUROC, AUPRC, *F*_1_-score, and/or Spearman Rho will be used to monitor differences between predicted outputs and true values across each epoch of training. Hyperparameter sweeps will be used to optimize the model’s performance and reduce overfitting risks. Sweeps will include adjustments to hyperparameters such as model width, model depth, learning rate, optimizer selection, learning rate schedulers, and early stopping. Model interpretability will be aided by methods such as Shapley Additive Explanations (SHAP) to identify key features relevant for clinical interpretation and application. Additionally, Phase 2 of this study is designed for prospective validation in a novel cohort, allowing for an assessment of the model’s validity beyond standard performance metrics.

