## Discussion

### Expected Findings

The purpose of this study is to develop a digital biosignature of the pain experience in youth and adolescents with chronic MSK pain. Self-report measures are the current gold standard for monitoring the pain experience and informing clinical decision-making. The purpose of developing a digital biosignature is to overcome the limitations of self-report, specifically the tendency to represent a single point in time and its inherent vulnerability to recall bias. A digital biosignature will provide real-time, objective measures of the pain experience through a holistic, multisystem lens.

This study is expected to result in several clinical benefits. First, the development and validation of digital clinical end points facilitates more robust assessment of novel therapeutics and treatment paradigms for youth with chronic MSK pain. The precise monitoring of treatment response would enhance the rigor and effectiveness of clinical trial design, leading to improved treatments, especially for those refractory to existing therapies. Second, a digital biosignature will give clinicians a deeper understanding of their patients’ individual pain experience through real-time, longitudinal monitoring of symptom fluctuations. These insights will enhance clinical decision-making and support a shift toward individually tailored interventions. Real-time tracking will also facilitate expedited shifts in a prescribed treatment plan, saving time and resources in helping patients to find the best treatment option for their specific pain presentation. Additionally, an objective biosignature may improve patients’ pain experience and interactions with clinicians by reducing the need to repeatedly recount severe pain events, an act that itself may be distressing. Finally, not only will a digital biosignature inform clinical practice, but it will also empower patients to have more control over their symptoms. Specifically, Phase 2 addresses this last point through enhanced “wellness alerts” for improved self-efficacy in living with chronic pain.

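### Nonwear indicators are inputs to the biosignature and only absolute accuracy is assessed, so the evaluation cannot separate watch physiology from wear behaviour

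*Protocol article*

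**What the plan says.** All references are to the protocol article.

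- **Handling Missing Data** gives the source of the gaps: "Missing data due to nonwear or sensor dropout will be handled using a hierarchical approach". Of daily features it says: "Daily features may be imputed using time-series–aware methods (eg, forward/backward filling within individuals". It then commits to the indicators: "Missingness indicators will be included as additional covariates in model development to account for information loss".
- **Outcome Measures** fixes the label: "The primary outcome used to validate the biosignature (ground truth) will be the participant’s self-reported onset of a pain flare".
- **Biosignature Development** sets the yardstick: "Model performance will be assessed using the area under the receiver-operator characteristic curve (AUROC", followed by AUPRC, the F1-score, Spearman's rho and/or Mann-Whitney tests. SHAP is planned as an aid to interpretation. No reference model is named, and neither is any difference from one.
- **Sample Size Justification and Power Analysis** describes a primary model of about 35 watch-derived features, secondary models that add demographics, pain history and task metrics, and splits by participant.
- **Smartwatch Metrics (Primary)** asks for at least 18 hours of wear a day, backed by notifications and weekly payment: "Those who do not meet adherence standards may not be eligible to receive a given week’s compensation". Participants who persistently fall short may be withdrawn.
- **Expected Findings** states the aim: "The purpose of developing a digital biosignature is to overcome the limitations of self-report". The section presents the result as an objective, multisystem measure.

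**The concern.** A missingness indicator derived from nonwear records behaviour. It does not measure heart rate, gait or sleep. Flares may affect that behaviour: participants are told that flares are typically disruptive, and patient partners reported that a flare can be too severe to log as it happens (Collaborations With People With Lived Experience). A participant in that state may also leave the watch off or uncharged.

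A model drawing partly on watch-off information would then earn AUROC and AUPRC that the article would report as the accuracy of an objective biosignature. Wear in this study is also partly produced by its prompts and payments, so any accuracy that depends on wear may not carry over to users without them. What is at stake is how the result can be described, and what is taken forward to the Phase 2 alerts.

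**Working it through.** The article gives no AUROC target, flare rate or nonwear rate, so there is no figure of its own to reproduce. The check has two parts.

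**1. Can the stated evaluation tell the two sources apart?**

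- *Inputs:* watch features plus missingness indicators.
- *Yardstick:* absolute agreement with the flare label. Two models with the same AUROC, one driven by physiology and one by wear, score identically.
- *Simple-to-deep model sequence:* this compares algorithms on the same inputs.
- *Secondary models:* these add inputs. None removes the watch measurements or the indicators.
- *SHAP:* this attributes the predictions of a fitted model. It does not give held-out performance without the wear signal, and no decision follows from it. Step and standing totals also fall when the watch is off, and filled values follow the gaps. SHAP would credit both to the feature and not to nonwear.

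So no stated step isolates the wear contribution.

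**2. How large could it be?** All inputs here are assumptions.

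Let p1 and p0 be the probability of a wear gap on flare-target days and on other days. For a yes/no flag used alone:

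AUROC = p1(1 − p0) + ½[p1·p0 + (1 − p1)(1 − p0)] = 0.5 + (p1 − p0)/2

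| p0 | p1 | AUROC of flag alone |
|---|---|---|
| 0.10 | 0.10 | 0.50 |
| 0.10 | 0.20 | 0.55 |
| 0.10 | 0.30 | 0.60 |
| 0.10 | 0.40 | 0.65 |
| 0.10 | 0.50 | 0.70 |

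Only the difference matters, so p0 = 0.20 or 0.30 with the same gaps gives the same values.

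If wear is entered as hours and is normally distributed with a shift of d standard deviations on flare days, AUROC = Φ(d/√2). For d = 0.25, 0.5, 0.75 and 1.0 this is 0.57, 0.64, 0.70 and 0.76.

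With no difference in wear, the contribution is nil (0.50). The documents do not say where in this range the study lies.

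**The case against.** The strongest reply has five parts.

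- **Missingness indicators are recognised practice.** This stands. Including them is not an error, and the point does not ask for their removal.
- **The target is onset, and the article says "Any windowing will only use past data relative to the prediction time to avoid leakage".** Watch removal caused by a flare comes after onset, so it should be excluded if the prediction time precedes onset. This narrows the route but does not close it. Data Reduction builds one daily feature vector and leaves the target's time scale to be chosen, with daily as its example. Nonwear on the day of the flare can therefore still enter, as can a change in wear before onset.
- **Incentives reduce nonwear.** They may, which would shrink the effect within this study. The question of transfer to other users remains.
- **Phase 2 validates in a new cohort.** It does, but the measures listed there are again absolute, so the ambiguity would persist.
- **A fuller plan or the preregistration may contain comparators.** That is possible, and the absence of a benchmark from a condensed article is not a fault in itself. The point rests on the combination the article does state: wear-derived inputs, absolute measures only, and a claim of objective measurement.

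Two stronger readings are tempting, and the documents support neither. A reader might infer that accuracy could come from recent symptom ratings. Those ratings are not listed among the primary model's inputs; the daily self-reports serve as ground truth. A reader might also infer that the biosignature must outperform self-report. The stated aim is to overcome burden, single-time-point assessment and recall bias, with self-report as the reference, so a watch model that merely matched recent ratings could still serve it.

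**Conclusion.** The point holds as a limit on interpretation. As written, the evaluation cannot say how much of the biosignature's accuracy comes from watch physiology and how much from whether the watch was worn. It does not show that accuracy will be inflated. That requires flares to be associated with wear at the chosen prediction time, which is plausible but not documented.

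On assumed differences in nonwear of 10 to 40 percentage points, a flag alone gives an AUROC of 0.55 to 0.70. The lower part of that range is modest by itself, but it is enough to blur the reading of a moderate headline figure. This is a cheap and worthwhile improvement to a development study and does not invalidate the design.

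**What to change.** Keep the missingness indicators. On the same participant-level splits and at the same prediction time, report:

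1. the primary watch model with the indicators;
2. the same model without them;
3. a wear-only model using missingness and wear-time indicators, day of week and study week.

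Give the differences in AUROC and AUPRC (1 minus 2, and 1 minus 3) with intervals obtained by resampling participants. The wear-only model is needed as well as the second fit, because wear-dependent totals and filled values can carry the nonwear signal even after the flags are dropped.

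State in the analysis plan that the biosignature will be described as physiological only to the extent that it improves on the wear-only model. This is a rule for wording the result; no pass/fail threshold is needed in a study that tests no specific hypothesis. A model built from the previous day's check-in scores may be shown as optional context, but not as a criterion.

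Wear hours are already collected, so the cost is a few extra fits and a few sentences. The drawback is that the headline accuracy may look less favourable beside the wear-only figure. Data collection and analysis were ongoing at the last report, so the comparison should be written down before the final models are fitted.

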#### Biosignature Development

Higher-level multivariate models will be developed, beginning with simpler traditional machine learning models before progressing to deep representation learning methods. Traditional machine learning algorithms will be trained using a nested k-fold cross-validation design. Model performance will be assessed using the area under the receiver-operator characteristic curve (AUROC), the area under the precision-recall curve (AUPRC), the *F*_1_-score, Spearman Rho, and/or Mann-Whitney tests of prediction outputs. Additionally, deep learning algorithms will be trained using train/validate/test sets where model loss, AUROC, AUPRC, *F*_1_-score, and/or Spearman Rho will be used to monitor differences between predicted outputs and true values across each epoch of training. Hyperparameter sweeps will be used to optimize the model’s performance and reduce overfitting risks. Sweeps will include adjustments to hyperparameters such as model width, model depth, learning rate, optimizer selection, learning rate schedulers, and early stopping. Model interpretability will be aided by methods such as Shapley Additive Explanations (SHAP) to identify key features relevant for clinical interpretation and application. Additionally, Phase 2 of this study is designed for prospective validation in a novel cohort, allowing for an assessment of the model’s validity beyond standard performance metrics.

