### Participants and Setting

Up to 500 youth and adolescents with chronic primary or secondary MSK pain [21,22] will be enrolled in this study. Individuals are eligible to participate if they are between 14 and 24 years old and experience MSK pain (pain in muscles, tendons, bones, joints) in one or more anatomic regions that has persisted or recurred for ≥ 3 months and is associated with significant emotional distress or functional disability. Individuals are excluded if they report only headache, orofacial, or visceral pain, have been hospitalized in the past 30 days for something other than pain, have a significant cognitive impairment that would prevent study participation (eg, severe brain injury), are currently undergoing treatment for cancer, or are pregnant or expect to become pregnant over the study period. This study is listed at ClinicalTrials.gov (NCT06867757) and preregistered on Open Science Framework (10.17605/OSF.IO/EN69C).

Participants are recruited nationwide through a multipronged recruitment strategy to ensure a representative sample. Recruitment within the Stanford health care system occurs through the Research Participation and Engagement Program (RPEP) and Stanford Children’s Health Pediatric Pain Management Clinic. Nationwide recruitment occurs through a custom-designed study website, community advertisements to pediatric multidisciplinary pain clinics in the United States, advertisements sent via postal mail, and patient advocacy networks (eg, US Pain Foundation, American Chronic Pain Association, and The Ehlers-Danlos Society). Interested participants are directed to complete a web-based study interest form as the first step of the eligibility screening. Potentially eligible participants are then contacted by the study team for additional screening based on the previously described eligibility criteria.

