Once the baseline surveys have been completed, the participants begin to receive “daily check-in” surveys, deployed at 5 pm (participant’s local time) and available to complete until 11:59 pm, for the duration of the 12-week study. Participants receive daily prompts through the app interface to complete these “daily check-in” surveys, which include short versions of self-report measures to quantify daily pain interference, pain, fatigue, mood, stress, sleep, and physical activity (Table 1). The daily check-in also asks participants to report whether they had a pain flare that day (“yes/no”) and to describe its characteristics. A pain-flare [10,11] is described to participants using the following language: “A temporary but noticeable worsening of your usual pain and/or symptoms (eg, fatigue, stiffness, and emotional distress) that feels more intense than what you typically deal with. Pain flares typically meet the following criteria: (1) are disruptive, (2) last longer than usual pain spikes, (3) affect more than just pain, (4) may be linked to a trigger, and (5) are bigger than normal pain changes.” Participants also have the option to initiate an unprompted retrospective or real-time pain flare report outside of the time-based daily check-in. The daily check-in also includes a daily diary for participants to note any exciting or stressful daily events (eg, academic stress, medical appointment) and any pain wellness strategies used (eg, deep breathing, pacing, journaling). The daily self-report measures are used as the gold standard (ie, ground truth) to which novel physiological markers are compared and thus are essential to ensure the clinical relevance of the biosignature.

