#### Sample Size Justification and Power Analysis

Given that the goal of this study is not to test a specific hypothesis, but rather to iterate over an entire data set to develop higher-level multivariate models, sample size and power analysis are less relevant for our study design. However, multiple strategies will be included to ensure data sufficiency. Collecting 12 weeks of daily self-reports and continuous smartwatch-derived features for up to 500 participants will enable multiresolution feature engineering while preserving participant-level separation during model evaluation (nested cross-validation, train-validate-test splits by participant). Outcome-event counts will be monitored to reduce overfitting risk. We expect to include approximately 35 Apple Watch–derived features (eg, physiological and physical function and sleep) in our primary model, alongside demographics (eg, age, sex, social determinants of health), pain-related features (eg, pain diagnoses, medical history), and task-based performance metrics (TSST-OL, 30s-STS) in secondary models. Model complexity controls, such as regularization, feature reduction, and early stopping, will be incorporated as needed. Furthermore, our sample of up to 500 participants will far exceed those found in comparable studies [20,44]. Achieving 80% of the target recruitment (ie, 400 participants) is also sufficient based on outcome-event counts and comparable studies.

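### The named performance measures do not separate ranking flare-prone youths from detecting change within a youth, and an ordinary Mann-Whitney test on pooled repeated rows would be anticonservative

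*Protocol article*

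**What the plan says.** All references are to the protocol article.

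- **Aim (Outcome Measures).** "A digital biosignature will be developed to enable the detection of a change in pain status". The primary ground truth is the participant's self-reported flare onset. Stratifying by demographic features and adjusting by partial correlation are both optional.
- **Rows (Data Reduction).** "All features derived at finer resolutions will be consolidated into a single daily feature vector". On the unit of evaluation: "The model prediction target and evaluation will be defined at a chosen time scale (eg, daily". Daily is an example, not a commitment.
- **Outcome reports (Self-Report Measures, paragraph after Table 1).** "The daily check-in also asks participants to report whether they had a pain flare that day". Unprompted flare reports are also possible.
- **Measures (Biosignature Development).** AUROC, AUPRC, F1, "Spearman Rho, and/or Mann-Whitney tests of prediction outputs". No unit of analysis, within-person version or cluster adjustment is given.
- **Clustering (Sample Size Justification and Power Analysis).** Folds and train-validate-test sets are split by participant. The same section gives the scale: "Collecting 12 weeks of daily self-reports and continuous smartwatch-derived features for up to 500 participants", with the fallback that "Achieving 80% of the target recruitment (ie, 400 participants) is also sufficient".

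**The concern.** Two separate matters follow from having many rows per youth.

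**What AUROC measures.** Pooled over all rows, AUROC compares each flare row with each non-flare row, and almost all such pairs come from two different youths. A score that carries only stable traits, such as resting heart rate or habitual activity, can rank flare-prone youths above others and earn an AUROC above 0.50 without telling one day from another in any youth. The stated aim, and the Phase 2 alerts meant to build on it, concern change within a youth. The secondary models add demographics, diagnoses and medical history. The main effects of these fixed features can raise a pooled AUROC but cannot order days within a person. Phase 2 plans AUROC, AUPRC and F1 again, with predictive values, so a trait-ranking model could replicate there without the distinction becoming visible.

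**What the Mann-Whitney test assumes.** Its usual p-value takes rows as independent. Days from one youth are correlated in both flare status and score, and keeping youths out of the training set does not change that.

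At stake is whether the reported performance can be read as evidence for the stated aim.

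**Working it through.** **There is no plan figure to reproduce.** The article states no alpha, power or target AUROC. Its arithmetic is consistent: 12 weeks × 7 = 84 days per youth, 500 × 84 = 42,000 rows at most, and 0.80 × 500 = 400.

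**Inputs.** From the article: 84 days and up to 500 youths. Assumed, because the article does not give them:
- flares on 20% of days (10% and 30% also tried);
- flare ICC of 0.05 to 0.30;
- score ICC of 0.1 to 0.8;
- correlation r between the score and the youth's own flare rate (on a normal-score scale) of 0.2 to 0.7.

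**Step 1: what pooled AUROC compares.** If each of N youths has *a* flare rows and *b* non-flare rows, there are N × a × b same-youth pairs among N² × a × b pairs in all, a share of 1/N. With N = 500 that is 0.2%. Pairs of different youths also reflect any genuine within-youth signal, so this alone does not make pooled AUROC uninformative. It does mean that stable differences between youths can drive it.

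**Step 2: pooled AUROC with no within-person signal.** Flares were simulated as beta-binomial over 84 days, with a score constant within each youth, so within-person AUROC is exactly 0.50. At 20% flare days:

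| r | ICC 0.05 | ICC 0.10 | ICC 0.20 | ICC 0.30 |
|---|---|---|---|---|
| 0.2 | 0.531 | 0.541 | 0.565 | 0.568 |
| 0.3 | 0.545 | 0.564 | 0.600 | 0.613 |
| 0.5 | 0.578 | 0.606 | 0.647 | 0.674 |
| 0.7 | 0.607 | 0.651 | 0.709 | 0.749 |

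At r = 0 the result is about 0.50. At r = 0.2 it stays below 0.60 at all three flare rates (0.531 to 0.579). At r = 0.5 it is 0.599 to 0.708 with 10% flare days and 0.566 to 0.658 with 30%. I re-ran the 20% rows with a separate simulation and they agreed to within about 0.01.

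When random day-to-day noise was added to the score (20% flare days, flare ICC 0.10 to 0.30, r of 0.5 or 0.7), pooled AUROC was 0.575 to 0.724. The AUROC computed per youth and then averaged was 0.49 to 0.51 throughout. The within-person version therefore tells the two situations apart.

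**Step 3: error of an ordinary Mann-Whitney test on pooled rows.** The score is unrelated to flares and the nominal level is 5%. The approximation is

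deff = 1 + (84 − 1) × ICC_flare × ICC_score, and true error = 2 × [1 − Φ(1.96/√deff)].

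Worked example with ICCs of 0.10 and 0.5: deff = 1 + 83 × 0.10 × 0.5 = 5.15; 1.96/√5.15 = 0.864; error = 38.8%.

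| Flare ICC | Score ICC | deff | Formula | Simulated, 500 youths | Simulated, 100 youths |
|---|---|---|---|---|---|
| 0.05 | 0.1 | 1.42 | 9.9% | 9.7% | 9.7% |
| 0.10 | 0.5 | 5.15 | 39% | 38% | 40% |
| 0.20 | 0.5 | 9.30 | 52% | 53% | 54% |
| 0.30 | 0.8 | 20.92 | 67% | 68% | 71% |

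Each simulated figure rests on 300 replicates. With flare ICC near zero the simulated error was 3% to 5%, so the excess comes from the clustering. The number of youths hardly matters.

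**Step 4: a coarser time scale.** With 12 weekly rows and ICCs of 0.10 and 0.5, deff = 1 + 11 × 0.10 × 0.5 = 1.55 and the error is about 12%. The problem shrinks but remains.

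**Step 5: redundancy.** The Mann-Whitney statistic U divided by n₁ × n₀ is the AUROC. The test adds only a p-value to a measure already listed.

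**The case against.** **Choices left open.** A reader might infer that the plan commits to daily evaluation and to treating up to 84 days per youth as independent. It does neither. The time scale is still to be chosen, the Mann-Whitney test ends an and/or list with no unit attached, and the unit or a cluster adjustment may stand in a fuller plan that is not shown. This objection stands, so the point about the test is conditional.

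**No decision rule.** A reader might also infer that the study could declare success on a false-positive test. The article says that it does not test a specific hypothesis and sets no alpha or success threshold. There is no such rule to corrupt, and that reading fails.

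**Assumed size.** No ICC, flare rate or correlation is in the article, and an AUROC of 0.60 is not a benchmark there. The simulations label flare days, whereas the primary ground truth is flare onset. Onset labels would probably lower both prevalence and ICC, and so the effect. This also stands.

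**Existing safeguards.** Slopes and rates of change may be among the features, fixed characteristics enter only secondary models, and Phase 2 will assess alert accuracy in a new cohort. These help, but none separates discrimination between persons from discrimination within a person. The optional adjustment removes at most the part that demographics explain.

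**Choice of metric.** Within-person AUROC as the sole primary measure is debatable. It drops youths without both outcomes, is noisy when onsets are few, and does not show whether one alert threshold suits everyone. That is a reason to report it beside the pooled measures, not to omit it.

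**Conclusion.** The concern holds in a limited form. The article defines a within-person target but names measures that, as listed, cannot show whether it was met, and splitting by participant does not cure this. This is a mismatch between stated choices, not merely a detail left to a fuller plan.

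Its size depends on assumed inputs. At 20% flare days and flare ICC 0.05 to 0.30, a score with no within-person signal gives a pooled AUROC of about 0.55 to 0.61 at r = 0.3, 0.58 to 0.67 at r = 0.5 and 0.61 to 0.75 at r = 0.7, but below 0.60 at r = 0.2. If rows are daily and the Mann-Whitney test is run unadjusted, its nominal 5% error is about 10% to 68% with 500 youths and score ICC 0.1 to 0.8. Both effects are probably smaller for onset labels.

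The question of what AUROC measures carries the weight; the test is the lesser part. As this is exploratory model development and the remedy lies in analysis and reporting, I rate it a cheap improvement, not a must-fix.

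**What to change.** 1. State the unit of evaluation and whether performance is pooled over participants.
2. Drop the Mann-Whitney test, or use a participant-level or cluster-robust form.
3. Give 95% confidence intervals for all performance measures from a bootstrap that resamples participants, not rows.
4. Report within-person AUROC, averaged over youths with at least one flare row and one non-flare row, beside pooled AUROC and AUPRC. Base any claim of detecting change on the within-person figure, and state how many youths contribute to it.
5. Report the gain over a benchmark that uses only the youth's own earlier flare frequency.

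The cost is analysis-plan wording and a few lines of code. No new data are needed, and the change can still be made while data collection continues. The downsides are that youths without both outcomes drop out of the within-person measure, intervals widen, and the headline figure may fall.
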